### Power for comparing rates of change in systolic blood pressure response over 12 months between groups

The power to detect a difference in slopes (β_1A_-β_1B_) over the twelve months of the study (using all waves of data) was examined. An estimate of the required sample sizes [64,65], is given, considering time measured as the duration between the first and jth occasion, j = 0, 0.5, 1 year. The assumptions above were used regarding design effects and reliability; these calculations assume that ρ = 0.5, 0.6 (the average correlation between baseline and follow up) and δ = 6, 7 (SBP = yearly point reduction). Based on examination of endpoint differences, the required sample sizes ranged from 175 to 225, depending on the assumptions regarding effect sizes [66]. The selected sample size of 225 per group permits detection of relatively small effect sizes, ranging from 5 to 6, depending on different scenarios.

#### Power for the stroke recurrence outcome at 24 months

Power was examined for stroke recurrence outcomes using the sample size formula for the log-rank test, where *d* is the expected probability of an event over subjects and is the hazard ratio. An additional calculation examining time-to-event using a Cox model was also performed. The assumptions were as above regarding reliability, cluster size and intracluster correlation coefficient. The correlation between pre- and post-measures was set at 0.60. A sample size of between 208 and 223 per group is needed, depending on the model and assumptions for 80% power to detect a 10% intervention group reduction in the rate of stroke at 24 months from a baseline rate of 15% [67].

#### Summary

Conservatively, under the assumptions specified above, 225 subjects per group will provide power ≥0.80 to detect the hypothesized 6 to 8 unit differential change in SBP, based on testing the Time X Group interaction in a mixed model, adjusting for unreliability, design effects due to clustering and serial correlations. This sample size will also provide power ≥ 0.80 to detect the hypothesized 10% group reduction in the rate of stroke at 24 months from a baseline rate of 15%.

### Analytic plan

#### Primary hypotheses: patients randomized to HBPTM + NCM will have (a) greater reduction in SBP at 12 months, and (b) lower rates of stroke recurrence at 24 months, compared to those in HBPTM alone

The analyses of SBP change will use mixed random effects models, and a full information maximum likelihood approach, with sensitivity analyses using generalized estimating equations. The change from pre- to post-treatment values of continuous outcomes will be modeled as functions of treatment group, time and the interaction of time and treatment. The intent-to-treat analyses performed using SAS PROC MIXED will permit modeling design effects (clustering), and allow for the possible group heterogeneity in residual variances and serial correlations that may require modeling to satisfy model assumptions and improve model fit. Based on prior analytic experience with the outcome variables, it is not expected that transformations will be necessary. Analyses of 24-month stroke recurrence will be performed using the log rank test or a Cox model examining time-to-event, should covariates be required.

Prior to analyses, baseline values of all variables from each arm will be examined; however, no *P* values will be provided, and covariates are not proposed for inclusion in the main analyses of treatment effects. If one or more sources of potential (selection or attrition) bias are identified, the predicted values from those analyses will be included as covariates in secondary analyses. Depending on the severity of missing data, other modeling techniques may be used.

Since the analysis and inference is based on intent-to-treat, an attempt will be made to obtain post-treatment data from all randomized participants, regardless of their adherence to the interventions. Nonetheless, secondary analyses will be conducted to investigate the impact of differential participation, stratifying participants in the treatment conditions based on their degree of participation and examining differences between strata on the outcome measures at follow-up.

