### Sample size and power analysis

The primary hypotheses are (a) a greater reduction in systolic BP over three waves of data: baseline, 6 and 12 months and (b) a lower 24-month stroke recurrence rate among the combined HBPTM + NCM group compared to the HBPTM alone group. Although there may be more than one episode of stroke per patient, given the sample size, we will combine all events. We assume separate analyses of the outcomes, with pre-specified α = 0.05 for each outcome. Statistical modeling procedures will be used that allow the inclusion in the analysis of participants who do not complete the follow-up assessment (on an intent-to-treat basis). The approach to the power calculations incorporates the design feature of clustering. The cluster size of participants who are eligible (uncontrolled hypertension with a history of stroke) within PCP is estimated to range from 5 to 6. Data from a similar study of telemedicine (IDEATel) delivered to New York City Hispanics and Blacks did not show heterogeneous variances [60], so this scenario was not included in power calculations. Specific types of selection bias and attrition were considered.

Based on studies of telemedicine in Blacks and Hispanics [42,43,60-62], it was estimated that the baseline and longitudinal standard deviations of SBP at baseline will be between 18 and 22 mm Hg. The observed mean differences were from 3 to 8 for SBP. We posited that the enhanced telemedicine intervention will result in an effect size ranging from a 6- to 8-point difference in SBP. The assumptions were as follows: α = .05 for a two-tailed test; 1-β = .80 and above; and δ = μ_1_-μ_2_ = 6, 7, 8 (SBP point reduction). The following assumptions were used in the power calculations: R = 0.90 (reliability); g = 2 (groups), pooled σ = 20.75 (baseline control: 19.6; intervention 19.2; 6 month control: 21.7; intervention: 20.5; 12 month control: 21.0; intervention: 22.3), d = δ/σ (where δ is difference in end study and d is Cohen’s d;) [63]. The cluster size was estimated as 5; the intracluster correlation (ICC) = 0.03; and Vif = 1+ (clustersize-1)*ICC = 1.12.

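### The primary SBP model leaves the baseline difference between arms free, giving up about 12 to 25% of the information on the 12-month contrast that baseline adjustment would recover at no cost

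*Protocol article*

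**What the plan says.** In the protocol article's Analytic plan (Primary hypotheses), changes in continuous outcomes "will be modeled as functions of treatment group, time and the interaction of time and treatment", fitted as a mixed model by full-information maximum likelihood. The next paragraph says that "covariates are not proposed for inclusion in the main analyses of treatment effects". Predicted values from any bias analyses enter only as covariates in secondary analyses.

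The Sample size and power analysis section counts baseline, 6 and 12 months as the three waves of SBP data. The Summary of that section bases the test on the time-by-group interaction and states that "225 subjects per group will provide power ≥0.80 to detect the hypothesized 6 to 8 unit differential change in SBP". The power section for SBP change notes that "these calculations assume that ρ = 0.5, 0.6 (the average correlation between baseline and follow up"). The Randomization section places randomisation after the baseline assessments.

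For the other primary outcome, stroke recurrence, the analysis is to be done "using the log rank test or a Cox model examining time-to-event, should covariates be required".

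**The concern.** When baseline is part of the outcome vector and the model has a group main effect, the two arms get separate baseline means. The 12-month treatment contrast is then a difference in change from baseline. Because baseline SBP precedes randomisation, the true baseline difference is zero by design, and a model that uses this fact is more precise. A model that does not use it also carries any chance baseline imbalance in full into the change contrast. At stake is the precision of a primary comparison, which could be improved with data the trial already collects.

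The stroke sentence sits awkwardly beside the no-covariates statement: one proposes no covariates in the main analyses, the other makes the choice of test depend on whether covariates turn out to be needed.

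**Working it through.** **Inputs**, all from the article's sample size and power sections:
- "α = .05 for a two-tailed test; 1-β = .80 and above"
- "an effect size ranging from a 6- to 8-point difference in SBP"
- "pooled σ = 20.75"
- wave SDs (control/intervention): baseline 19.6/19.2, 12 months 21.0/22.3
- ρ = 0.5 and 0.6
- design effect 1 + (5 − 1) × 0.03 = 1.12
- reliability R = 0.90
- 225 per group

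The article does not say how R enters. I read it as multiplying the variance by 1/0.90. Complete data are assumed throughout.

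**Formulas.** With SDs s0 (baseline) and s12 (12 months) and n per arm, the variance of the 12-month contrast is:
- baseline difference free: (2/n)(s0² + s12² − 2ρ·s0·s12), which is (2/n)·2σ²(1 − ρ) when SDs are equal
- baseline means equal, or baseline as covariate: (2/n)·s12²(1 − ρ²)

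With equal SDs the ratio of the second to the first is (1 + ρ)/2, so the loss is (1 − ρ)/2. Power is Φ(δ / (SE·√(1.12/0.90)) − 1.96), where √(1.12/0.90) = 1.1155.

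**The plan's own figure first (model as written, equal SDs).** At ρ = 0.5, SE = √(4 × 20.75² × 0.5 / 225) = 1.956. At ρ = 0.6, SE = 1.750. Power for 6 mm Hg is 0.826 and 0.900 with the design effect only, and 0.785 and 0.867 with R as well. The detectable difference at 80% power runs from 5.2 to 6.1 mm Hg across these cases, against the article's 5 to 6. The stated power of at least 0.80 is therefore reproduced to within 2 points at worst.

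**Loss with equal SDs (pooled 20.75).**
- ρ = 0.5: SE 1.956 free, 1.694 adjusted. Variance ratio 0.75, loss 25%. Power at 6 mm Hg: 6/(1.956 × 1.1155) − 1.96 = 0.79, giving 0.785; 6/(1.694 × 1.1155) − 1.96 = 1.215, giving 0.888.
- ρ = 0.6: SE 1.750 free, 1.565 adjusted. Variance ratio 0.80, loss 20%. Power 0.867 and 0.930.

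At ρ = 0.5, 2(1 − ρ) = 1, so the model as written is no more precise than comparing 12-month SBP alone.

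**Loss with the article's wave-specific SDs.** Averaging variances over arms gives s0² = (384.16 + 368.64)/2 = 376.40 and s12² = (441.00 + 497.29)/2 = 469.15, so s0·s12 = 420.2.
- ρ = 0.5: n × variance is 2(376.40 + 469.15 − 420.2) = 850.6 free and 2 × 469.15 × 0.75 = 703.7 adjusted. Loss 17.3%; power 0.790 to 0.860.
- ρ = 0.6: 682.6 free and 2 × 469.15 × 0.64 = 600.5 adjusted. Loss 12.0%; power 0.870 to 0.909.

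**Other structures.** If time is fitted as a linear slope, generalised least squares gives losses of 27.3% and 21.4% (equal SDs) or 19.9% and 13.6% (wave SDs). If correlation decayed serially (my assumption: AR(1) with 6-month correlation 0.5 or 0.6, equal SDs), the 12-month loss would be 37.5% and 32.0%. The article states no such structure.

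**The case against.** The best defence is that the planned model matches its endpoint. The primary outcome is within-patient change, the power is built on the time-by-group interaction, and under randomisation the test is unbiased and keeps its type I error. All of that stands. Baseline SBP is also not ignored, since it is one of the outcome waves. But with a free baseline difference and complete data the 12-month contrast is still the plain change-score contrast, so that use brings none of the gain computed above.

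A reader might infer four stronger points. The documents do not support them:
- *That 20 to 25% is lost outright.* This requires equal SDs at baseline and 12 months. The article's own wave SDs bring the loss down to 17% and 12%.
- *That the trial is underpowered for SBP without adjustment.* The only figure below 0.80 for 6 mm Hg, 0.785, needs R read as a variance inflation on top of the design effect. With the design effect alone, power is 0.826 or 0.900; with neither factor it is 0.866 or 0.929. Randomisation is within physician, so 1.12 is itself pessimistic for this contrast.
- *That the primary stroke test is left open to choice after baseline data are seen.* The sentence is loose, but the statement that covariates are not proposed for the main analyses largely settles it in favour of the log-rank test.
- *That site should enter the primary models.* The section on mediators and moderators gives a reason for not stratifying by site, and nothing here shows a benefit from overriding it.

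It is also fair that the free baseline difference is inferred from the listed terms: the article does not say in words that baseline means are unconstrained. A fuller plan could contain the constraint, but the listed group effect and the no-covariates sentence point the other way.

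**Conclusion.** The point holds as a matter of efficiency. The SBP model as stated gives up 25% and 20% of the information on the 12-month contrast at ρ = 0.5 and 0.6 if SDs are equal, or 17% and 12% with the article's wave-specific SDs. For a 6 mm Hg difference, this is worth about 6 to 10 points of power at ρ = 0.6 and 0.5 with equal SDs, and 4 to 7 points with the wave SDs. These figures assume complete data, equal correlations between waves, and R acting as a variance inflation. They do not show bias, an inflated type I error or a wrong sample size. The stroke wording is a lesser matter of consistency.

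**What to change.** In the primary mixed model, constrain the baseline SBP mean to be equal across arms, or include baseline SBP as a covariate with 6 and 12 months as outcomes. Amend the no-covariates sentence to except baseline SBP. For stroke recurrence, state that the log-rank test is the primary analysis and that any covariate-adjusted Cox model is secondary, and delete the closing conditional clause about covariates. Leave the unstratified treatment of site as it is. The cost is a few lines of wording and model code. No new data are needed and the sample size does not change.

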### Treatment fidelity

Our efforts to maximize the quality and consistency of the interventions include (1) careful training of patients in the use of the home BP monitors; (2) strategies to enhance patient adherence to each of the interventions (that is, reminder calls, monitoring transmission of home BP readings, weekend availability for NCM sessions); and (3) monitoring of adherence to the interventions to evaluate consistency across study sites and, for the HBPTM + NCM arm, across nurses. A key strength of this study is the use of an established, successful NCM intervention that does not require extensive training or supervision from research staff, aside from details of the study protocol. The nurses working with the House Calls program have undergone extensive training in principles and strategies of behavior change needed for effective counseling of chronic disease patients (for example, motivational interviewing skills, problem-solving approaches). To provide data on intervention content for secondary analyses, the nurses complete a checklist following each counseling session to indicate the topics covered.

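### The participation analysis compares outcomes between strata formed after randomisation and calls the result an impact; it could show a spurious difference in either direction and should be descriptive only

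*Protocol article*

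**What the plan says.** The Protocol article's analytic plan for the primary hypotheses puts intent-to-treat first: "Since the analysis and inference is based on intent-to-treat, an attempt will be made to obtain post-treatment data from all randomized participants". It then adds that "secondary analyses will be conducted to investigate the impact of differential participation", and gives the method: "stratifying participants in the treatment conditions based on their degree of participation and examining differences between strata on the outcome measures at follow-up".

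The plan does not call this comparison descriptive, and it names no step that keeps the randomised contrast. The preceding paragraph lets predicted values enter secondary analyses as covariates, but only if selection or attrition bias has been identified.

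Three other sections bear on the point:
- The background section says that poor adherence to antihypertensive medication is associated with death after stroke.
- The section on the combined intervention sets out weekly, then biweekly, then monthly calls over 12 months and lets nurses add calls at their discretion.
- The treatment fidelity section provides for "monitoring of adherence to the interventions to evaluate consistency across study sites" and for a checklist after each counselling session. This is not an error; it shows that participation data will exist.

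**The concern.** Patients who keep up with calls and readings may differ from those who do not in medication-taking, health, mood and access to care, all of which can also affect blood pressure. A difference between participation strata mixes those traits with any effect of the intervention. The method is stated outright, so this is not a detail left to a later document.

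The stroke outcome has a second problem. Calls run to month 12 and strokes are counted to month 24, so a patient who has an early stroke may stop participating because of it. Low participation is then partly a consequence of the outcome.

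At stake is how the secondary result is read. A between-strata difference presented as the impact of participation could be taken as evidence of what NCM does when fully delivered, whatever the randomised comparison shows.

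**Working it through.** **Inputs from the plan.** The power section gives "α = .05 for a two-tailed test; 1-β = .80 and above", "R = 0.90 (reliability); g = 2 (groups), pooled σ = 20.75" and "the intracluster correlation (ICC) = 0.03; and Vif = 1+ (clustersize-1)*ICC = 1.12"; the slope section adds "these calculations assume that ρ = 0.5, 0.6 (the average correlation between baseline and follow up". There are 225 patients per group, a hypothesised SBP difference of 6 to 8 mm Hg, and a stroke rate of 15% with a 10% reduction, read here as percentage points. The plan gives no figure for the participation analysis itself.

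**What 20.75 is.** The root mean square of the six SDs listed in the power section is √(2582.23/6) = 20.75. It is therefore an SD of SBP values. The SD of change is 20.75 × √(2(1 − ρ)): 20.75 at ρ = 0.5 and 18.56 at ρ = 0.6.

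**Reproducing the design figure.** Effective n = 225 × 0.90/1.12 = 180.8 per group. For 6 mm Hg at ρ = 0.5, SE = 20.75 × √(2/180.8) = 2.18 and power = Φ(6/2.18 − 1.96) = 0.785; at ρ = 0.6 it is 0.867. For 7 and 8 mm Hg, power is 0.89 to 0.98. This agrees with the stated 0.80 or more to within 2 points, so the inputs are read as intended.

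**Assumed inputs, not in the plan.** The correlation r between propensity to participate and lower SBP is taken from −0.2 to 0.3. Strata are formed by a median split, and NCM has no effect.

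**SBP, strata comparison.** For a normal propensity split at the median, the two halves differ by 2 × φ(0)/0.5 = 1.596 SD. The expected spurious difference is r × SD × 1.596.

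| r | SD 20.75 | SD 18.56 |
|---|---|---|
| 0 | 0 | 0 |
| 0.1 | 3.3 | 3.0 |
| 0.2 | 6.6 | 5.9 |
| 0.3 | 9.9 | 8.9 |

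At r = −0.1 and −0.2, with SD 20.75, it is −3.3 and −6.6 mm Hg, an apparent harm.

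Within one arm of 225, the SE of the median-split contrast is about 20.75 × √(2/112.5) = 2.77. At r = 0.2 the chance of a two-sided 5% result is about Φ(6.62/2.77 − 1.96) = 0.67. Simulation with 20,000 trials per scenario gave about 22%, 67% and 96% at r = 0.1, 0.2 and 0.3.

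**SBP, randomised comparison.** In the same null simulations at r = 0.2 and 50% participation, the intent-to-treat difference averaged 0.0 with about 5% rejections, and the complier-average estimate (intent-to-treat difference ÷ uptake) averaged 0.0. With a true effect of 6 mm Hg in participators only, the strata contrast averaged 12.6 (6.6 + 6) and the complier-average estimate 6.0. That last agreement follows from giving non-participators no effect; it illustrates the method and does not test its assumptions in this trial.

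**Stroke.** Assume no NCM effect, no confounding, a constant hazard λ = −ln(0.85)/24 = 0.00677 per month, and that a stroke ends participation. The schedule implies about 8 + 4 + 8 = 20 calls. Let high participation mean at least 16 calls, reached at month 8, and let 50% of patients otherwise be high participators.
- High stratum: 1 − exp(−16λ) = 10.3%.
- Stroke before month 8: 1 − exp(−8λ) = 5.3%.
- Low stratum: (0.5 × 0.15 + 0.5 × 0.053)/(0.5 + 0.5 × 0.053) = 19.3%.
- Spurious gap: 9.0 points.

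With cut-offs at months 4 to 8 and 50% to 70% high participators, the gap runs from 4.5 points (12.7% against 17.2%) to 14.0 points (10.3% against 24.3%).

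**Precision of the alternative.** The 95% half-width of the complier-average estimate is 1.96 × 20.75 × √(2/225) ÷ uptake: 7.7, 5.5 and 4.3 mm Hg at 50%, 70% and 90% uptake. With the plan's inflation factor of 1.12 these become 8.1, 5.8 and 4.5.

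**The case against.** The best defence is that inference rests on intent-to-treat, outcomes are sought whatever the adherence, and the strata analysis is secondary. No primary hypothesis or power claim depends on it, and nothing says it will decide how much NCM is needed. All of that stands: the main conclusions are not at risk.

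A reader might infer that the analysis would show a large benefit of participation even if NCM did nothing. The document does not support this. The correlation that sets the size is not given, and at zero there is no bias. Because nurses may add calls at their discretion, call counts could be higher in poorly controlled patients, which would reverse the sign. An unknown sign does not make the contrast interpretable, however.

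The conditional covariate provision is a partial answer at most. It covers identified selection or attrition bias, not the reasons for participating, and cannot adjust for causes that were not measured.

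A reader might also infer that a complier-average analysis should replace the strata comparison altogether. That goes too far. The plan speaks of a graded degree of participation across the treatment conditions, and home monitoring occurs in both arms. The exclusion restriction is also strained: patients below a call threshold still receive some calls, nurses see home readings, review laboratory results and contact physicians, and alarm messages go to different staff by arm.

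The early nurse contact in the HBPTM-alone arm concerns the device and the educational materials. Scheduled counselling calls are described only for the combined arm, so treating non-uptake of counselling as one-sided is reasonable.

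**Conclusion.** The point holds as a fault in a stated secondary analysis. The strata are formed after randomisation, the wording is causal, and following the plan as written can give a confounded SBP result and a reverse-causal stroke result.

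Under a null NCM effect, the spurious SBP difference is about 3 to 10 mm Hg for an assumed r of 0.1 to 0.3, comparable with the hypothesised 6 to 8 mm Hg. For stroke, the illustrative gap is 9.0 points (range 4.5 to 14.0), against a design difference of 10. These sizes rest on the assumed correlation, the median split, the participation rates and cut-offs and, for stroke, on an event ending participation. They show what could happen and do not predict the direction.

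**What to change.** 1. Report outcomes by participation stratum as descriptive tabulations only, without between-strata tests, and remove the causal wording. Define degree of participation for each arm before outcomes are analysed.
2. Base any causal statement about NCM uptake on an estimator that keeps the randomised comparison. One option is a complier-average effect with randomised arm as the instrument for receipt of scheduled NCM counselling calls. Set the uptake definition in advance: for example, any counselling call, not counting the early device contact that both arms receive. Use higher call thresholds as sensitivity analyses, because patients below a threshold still receive some NCM.
3. State that this estimate covers NCM counselling only. Home-monitoring use occurs in both arms and stays descriptive.

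The cost is a few lines of text and a short analysis from session notes and checklists already planned. The downsides are the wider interval at low uptake and dependence on the exclusion restriction, which should be stated beside the result.
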